### Sample Size Calculation and Power

A minimum of 92 and maximum of 122 participants will be enrolled and randomized in this study (*n* = 46–61 per group). As OSA prevalence is 2-fold greater in males than females over the age of 50 (64–66), we expect to enroll males at a 2:1 ratio to females. However, we will not restrict enrollment based on sex.

In our preliminary study (49), the effect sizes (ESs) for SBP, PNE, and 24-h SBP were 2.50, 1.25, and 0.63. The within individual standard deviation (SD) was set to be the larger of the SDs for the two groups, although differences in SDs across groups were not substantial. If 45 participants per arm complete the main study, we will have over 80% power for any outcome with an ES > 0.63. Sex-specific comparisons of mean change scores between IMST groups can detect an ES > 1.19, provided at least 30 females complete the study (i.e., 75% of 1/3 of the initial sample size of 122), with at least 15 in each arm. This calculation includes a Bonferroni correction of the significance level—that is, the sex-specific comparisons are conducted at the 2.5% significance level.

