### Randomization, Blinding, and Treatment Allocation

Participants will be randomized after completing baseline assessments. Assignment to the training program will be by an unblinded Senior Research Professional. The study statistician will use a computer-generated randomization list for the study. Block randomization with block sizes of 2, 4, and 6 will be used to randomize participants into two groups (high- vs. low-resistance IMST) in a 1:1 ratio. Randomization will be stratified by sex (M/F) and OSA disease severity (moderate/severe). The randomization list will be stored in a .CSV file with the randomized group assignment hidden and only revealed by the Senior Research Professional at the time of randomization. Assignment to groups will be sequentially within strata.

Randomization will, on average, balance CPAP users (Yes/No) between the two arms within sex and severity strata however, the effect of treatment may differ depending on CPAP use. We will account for the potential effect of CPAP on outcomes, and possible interaction with treatment, by including CPAP and treatment-by-CPAP interaction effects in the mixed effects models. Based our pilot trials, we anticipate ~10–15% CPAP users in our study sample. The power to detect either a CPAP or a treatment-by-CPAP interaction, that is, our ability to tease out CPAP from IMST effects, will depend on the treatment-by-CPAP cell sample sizes and effect sizes.

Outcomes assessors and data analysts will be blinded to training group allocation. As both training programs have the potential to affect outcome measures, neither is considered a “placebo.” Subjects will be blinded to their allocation group.

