### Statistical Analysis

The same statistical approach will be used to address all hypotheses, as each hypothesis uses data collected on continuous outcomes (e.g., casual and 24-h BP) from a two-arm design with multiple time points. A standard repeated measures (with the number of time points depending on outcome) mixed model analysis of variance will be used to estimate average change from baseline within arms. Models will adjust for stratification on OSA severity, sex, and age. Subject specific random effects will be used to account for the repeated measures on an individual. Inferences will be based on available data using maximum likelihood, which accommodates data missing at random. We propose a within-individual analysis for the study (comparisons between arms will be based on average change from baseline vs. average at endpoint) as the correlations between baseline and 6-week SBP and plasma norepinephrine in our preliminary data were ~0.60 or larger (49). Effect sizes and confidence intervals will be reported in addition to *p*-values. Unless otherwise mentioned, tests will be two-sided and conducted at the 5% significance level.

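### Arms are compared on change from baseline without adjusting for the baseline value. At the plan's correlation of about 0.60 or larger, adjustment would cut the variance by up to about 20% (equal SDs assumed).

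*Protocol article*

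**What the plan says.** The Statistical Analysis section of the protocol article applies one approach to all hypotheses. A repeated-measures "mixed model analysis of variance will be used to estimate average change from baseline within arms". For the between-arm question, "comparisons between arms will be based on average change from baseline vs. average at endpoint". I read this as a choice of change over the endpoint mean. The reason given is that "correlations between baseline and 6-week SBP and plasma norepinephrine in our preliminary data were ~0.60 or larger".

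On covariates, "Models will adjust for stratification on OSA severity, sex, and age". The section on randomization, blinding and treatment allocation adds CPAP use by "including CPAP and treatment-by-CPAP interaction effects in the mixed effects models". Neither list contains the baseline value of the outcome, and nothing says that the two arms share a baseline mean. Randomization is stratified by sex and OSA severity, not by baseline blood pressure.

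On size, the section on sample size and power states: "If 45 participants per arm complete the main study, we will have over 80% power for any outcome with an ES > 0.63". The effect sizes quoted from the pilot are 2.50 for casual SBP, 1.25 for plasma norepinephrine and 0.63 for 24-h SBP.

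**The concern.** The article gives both the choice of contrast and the reason for it, so this is not a detail left to an analysis plan that is not shown. The reason supports less than it is used for. A correlation above 0.5 favours change over the endpoint mean when the SDs are equal, but those are not the only two options. Every participant has a baseline value, and in a randomized trial the contrast can be adjusted for it.

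The planned model does not do this by itself. If each arm has its own free baseline mean, then with complete data the arm-by-time contrast equals the difference in mean change. Main effects of sex, severity and age leave that contrast unchanged.

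Two things are at stake. One is precision, mainly for 24-h SBP, which has the smallest planning effect. The other is protection against chance baseline imbalance: a change score over-corrects for baseline, so an arm that starts higher by chance appears to fall more.

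**Working it through.** **Inputs.** From the protocol article: r about 0.60 or larger (casual SBP and norepinephrine, 6-week pilot), 45 completers per arm, effect size (ES) 0.63, two-sided 5%. Assumptions: equal SDs at baseline and follow-up; ES 0.63 is on the change-score scale (the article speaks of a within-individual SD); and an r of 0.6 to 0.8 for 24-h SBP, for which no correlation is given.

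**1. The plan's own figure.** With 45 per arm, ES 0.63 and two-sided 5%, power is 84.0% (noncentral t) or 84.8% (normal approximation). The claim of over 80% reproduces.

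**2. Variances.** Per participant, in units of the outcome variance:

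- endpoint mean: 1
- change score: 2(1 − r)
- baseline-adjusted: 1 − r²
- ratio of adjusted to change: (1 − r²) / [2(1 − r)] = (1 + r)/2

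| r | Change | Adjusted | Reduction |
|---|---|---|---|
| 0.5 | 1.00 | 0.75 | 25% |
| 0.6 | 0.80 | 0.64 | 20% |
| 0.7 | 0.60 | 0.51 | 15% |
| 0.8 | 0.40 | 0.36 | 10% |
| 0.9 | 0.20 | 0.19 | 5% |

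The plan's argument is the comparison of 0.80 with 1.00 at r = 0.60. The adjusted value of 0.64 is below both.

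**3. Cost of estimating the slope.** The variance inflation is about 1 + 1/(2×45 − 4) = 1.012. In a simulation of 20,000 trials with 45 per arm and r = 0.60, the reduction was 19.1% against the theoretical 20%.

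**4. Power.** The effect size becomes 0.63/√[(1 + r)/2]. Noncentral t, 45 per arm, 87 degrees of freedom:

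- r = 0.6: 0.63/√0.80 = 0.704, power 91.1%
- r = 0.7: 0.63/√0.85 = 0.683, power 89.4%
- r = 0.8: 0.63/√0.90 = 0.664, power 87.6%

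At r = 0.60, the number per arm for 80% power falls from 41 to 33.

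**5. Unequal SDs.** Let q be the baseline SD divided by the follow-up SD. The change-score variance is then 1 + q² − 2rq, and the adjusted variance stays at 1 − r². At r = 0.60:

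- q = 0.6: 0.64 against 0.64, reduction 0%
- q = 0.8: 0.68 against 0.64, reduction 6%
- q = 0.9: 0.73 against 0.64, reduction 12%
- q = 1.1: 0.89 against 0.64, reduction 28%

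In large samples the reduction is never negative.

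**6. Chance imbalance.** With equal SDs the slope of change on baseline is −(1 − r), which is −0.40 at r = 0.60. Each 1 mmHg by which one arm starts higher by chance moves the expected change-score difference by 0.4 mmHg towards a larger fall in that arm. The correlation of change with baseline is −√[(1 − r)/2] = −0.45.

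**The case against.** The strongest reply is that nothing here is an error. Comparing change between randomized arms is unbiased, preferring it to the endpoint mean at r above 0.5 is correct, and the power statement holds. All of that stands. So does the reply that the primary outcome hardly needs the gain: with a pilot effect size of 2.50 for casual SBP, adjustment only tightens the interval.

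Three limits on the size also stand:

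- The plan says 0.60 or larger, so with equal SDs 20% is about the most its own figure supports. The pilot correlation spans 6 weeks and the trial 24; a lower correlation over the longer period would raise the gain, but the article gives no 24-week figure.
- No correlation is stated for 24-h SBP, where the power gain matters most.
- Eligibility limits screening SBP to roughly 120–160 mmHg. This could narrow the baseline SD of casual SBP and shrink the gain.

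It could also be said that a baseline term may sit in an analysis plan that is not shown. The article does not exclude one, but its stated rationale makes an unadjusted change score the natural reading.

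A reader might go further and infer from "Subject specific random effects will be used to account for the repeated measures on an individual" that a single common correlation is imposed on all visits, so that the standard error is too small and the type I error too high. The article does not support this. It does not say that the random effects are limited to an intercept. Even if they were, the direction of any error depends on an assumed pattern. Take a correlation of 0.60 between baseline and the post-intervention visit, where the correct standard error is proportional to √(1 − 0.60), and let a common correlation equal the mean over the six pairs of visits:

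- Exponential decay in weeks (visits at 0, 25, 29 and 37): mean correlation 0.696, and √(0.304/0.40) = 0.87, so 13% too small.
- First-order decay by visit order: mean correlation 0.456, and √(0.544/0.40) = 1.17, so 17% too large.

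**Conclusion.** The point holds as a matter of efficiency. The plan's reason for using change scores does not address the better option of adjusting for baseline. With equal SDs, that option has 20% less variance at r = 0.60, 15% less at 0.7 and 10% less at 0.8, and the gain is smaller if the baseline SD is narrower than the follow-up SD. Under the two further assumptions about 24-h SBP, power with 45 per arm goes from 84% to about 88–91%.

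Two stronger readings should be avoided. The planned analysis is not biased or underpowered: it is valid under randomization and its power figure reproduces. Nor does adjustment strictly win in every case: at r = 0.60 it only ties with the change score when the baseline SD is 0.6 of the follow-up SD, and at r = 0 it ties with the endpoint mean.

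**What to change.** In Statistical Analysis, replace the sentence on between-arm comparisons with wording such as: *The treatment effect is the between-arm difference at 24 weeks, estimated from the longitudinal mixed model with baseline means constrained to be equal across arms, adjusted for sex, OSA severity and age. Within-arm change from baseline is reported descriptively.* An acceptable alternative is to enter the baseline value of the outcome as a covariate, with its own coefficient at each visit.

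The change needs one paragraph and one degree of freedom, about 1% of variance with 45 per arm. It needs no extra participants, visits or measurements. It should be made before the data are unblinded.

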## Adherence

Successful adherence is defined as a study subject who achieves an adherence rate of at least 70% (i.e., completes at least 74 of the 106 training sessions and attends 10 of 14 in-person training sessions).

## Data Management

Data will be collected manually and or with case report forms (CRF) and source documents. CRFs are defined as an electronic document used to record all protocol relevant subject information. CRFs will generated and accessed through REDCap. CRFs are specific to each visit and will be completed for each subject. Research personnel responsible for visits will be required to complete the appropriate report form in an accurate and concise manner. Source documents are raw data documents where clinical observations are initially recorded. This includes laboratory reports, device reports, and physical examination reports. Information will be entered in CRF so that it follows what is included in source documents.

After the completion of a CRF, data will be exported into a master spreadsheet for analysis using a double-entry method. All data included in this sheet will be de-identified. Manually recorded data will be entered into a digital master data file within 1 week of data collection by the investigator who collected the measure. Data that has been acquired digitally (e.g., FMD_BA_, PWV_CF_) will be checked for completeness immediately after collection and then stored for later analysis. Data recorded at baseline, post-intervention, and follow-up for each subject will be analyzed individually after that subject completes all follow-up testing sessions to ensure within-subject accuracy.

## Data Monitoring

This study will have a Safety Officer who is completely independent of the sponsor. The Safety Officer is a physician-investigator with extensive experience in clinical trials on MA/O adults and adults with hypertension. The Safety Officer will meet with the Study Oversight Team at regular intervals (at least twice yearly), with one in-person meeting and the other *via* teleconference, to review enrollment progress, safety data, data quality, and the primary efficacy endpoints.

## Anticipated Results

### Primary Hypothesis

Twenty-four weeks of high-resistance IMST will lower casual SBP in MA/O adults with above-normal BP and OSA by an average of 15 mmHg; some BP reduction will persist after 4, but not 12 weeks of free living. Adherence to IMST will be high (>80% sessions).

### Other Hypotheses

Twenty-four weeks of high-resistance IMST will:

Lower 24-h, daytime, and nighttime SBP, as well as PNE.Improve large elastic artery stiffness (i.e., PWV_CF_ reduction), NO-mediated EDD capacity, and *ex vivo* ROS production.Reduce superoxide-related suppression of NO-mediated EDD (as assessed by FMD_BA_ with Vitamin C infusion).Cause no change in EID (assessed as brachial artery dilation to sublingual nitroglycerin) indicating any improvements in FMD_BA_ observed are due to improvements in vascular endothelial function rather than increased vascular smooth muscle sensitivity to NO.Lower casual DBP and 24-h, daytime, and nighttime DBP.

Some effects will persist after 4, but not 12 weeks of free living.

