#### Other Outcomes

##### Endothelial Dependent Dilation

EDD will be assessed *via* brachial artery flow-mediated dilation (FMD_BA_) using high-resolution ultrasonography (Canon Xario 200G) (52, 56), the gold-standard *in vivo* measure of conduit artery vascular endothelial function, that is primarily mediated by NO. FMD_BA_ will be assessed by measuring brachial artery diameter and blood velocity at baseline and for 3 min following reactive hyperemia induced by 5 min of forearm blood flow occlusion with a cuff placed on the upper forearm and inflated at least 50 mmHg above SBP.

Data will be expressed as both percent and absolute (mm) change in arterial diameter from baseline (pre-cuff inflation diameter). Shear area-under-the-curve up to peak diameter will be calculated, and if group- or timepoint-differences exist, FMD_BA_ will be adjusted accordingly. Brachial artery diameter and blood velocity will be analyzed offline with commercially available software (Brachial Analyzer, Medical Imaging Applications LLC, Coralville, IA, USA). Peak arterial diameter will be compared to baseline diameter to calculate absolute change (mm) and percent change in diameter in response to the forearm hyperemic stimulus at baseline, after the 24-week training period, and at 4- and 12-weeks post-intervention.

To determine tonic oxidative stress-mediated suppression of endothelial function, FMD_BA_ will be repeated after intravenous infusion of supratherapeutic concentrations of the potent ROS-scavenging antioxidant, Vitamin C, and isovolumic saline infusion, as described previously (57, 58). A bolus of 0.06 g Vitamin C/kg fat-free mass dissolved in 100 mL of saline will be infused by IV at a rate of 5 mL/min for 20 min, followed immediately by a drip infusion of 0.02 g/kg fat-free mass dissolved in 30 mL saline infusion at a rate of 0.5 mL/min. FMD_BA_ will be performed after the bolus dose, during the drip infusion. FMD_BA_ with infusions will be performed at baseline, after the 24-week training period, and at 4- and 12-weeks post-intervention.

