##### Arterial Stiffness

Arterial stiffness will be assessed *via* carotid-femoral pulse wave velocity (PWV_CF_) using a transcutaneous tonometer (SPT-301 ADInstruments, Colorado Springs, CO) placed sequentially in position at the carotid and femoral arteries, with simultaneous electrocardiograph (ECG) recording (59). PWV_CF_ will be calculated as mean distance/transit time. Transit time will be determined as the time between the ECG R-wave and carotid pulse subtracted from the time between the ECG R-wave and femoral pulse. Thirty consecutive pulse waves from each arterial site will be analyzed and averaged. PWV_CF_ will be calculated from difference in carotid-sternal and femoral-sternal distance (m) divided by difference in transit time (s). PWV_CF_ will be assessed at baseline, after the 24-week training period, and at 4- and 12-weeks post-intervention.

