We do not expect any significant problems with these well-established training procedures that we have successfully employed previously (49, 52). In light of our previously published outcomes with IMST, our focus will be on outcomes for resting (casual) SBP (primary) and 24-h ambulatory SBP (secondary). FMD_BA_ and PWV_CF_ are strong independent predictors of incident CVD in MA/O adults (72, 73). Therefore, each of these vascular outcomes are important clinically as intermediary therapeutic targets of vascular disease. Measures of clinical CVD endpoints could be incorporated into a subsequent larger, more comprehensive, multi-site clinical trial. Although our ability to interrogate mechanisms of action in a definitive manner in all cases is limited, we have: (1) proposed mechanistic assessments based on findings from our foundational preclinical work in healthy young adults and (2) proposed to focus on assessments of NO-mediated vascular EDD because our pilot studies in MA/O adults without OSA support these as primary mechanisms (52). Last, recent prevalence estimates suggest >80% of adults >50 years exhibit age-related increases in aortic stiffness (elevated PWV_CF_) and/or hypertension (74) that is correlated with OSA severity (14). Thus, we anticipate a majority of subjects will exhibit aortic stiffening at baseline, and will benefit from IMST.

This study will assess the efficacy of long-term IMST in adults with OSA. Successful completion of this study will allow us to determine: (1) the extent to which IMST can lower BP over 24 weeks; (2) the degree of adherence to IMST when performed at home, 5 days/week, for 24 weeks; (3) persistence of training effects after cessation of IMST; and (4) the mechanisms driving IMST-induced reductions in BP, including effects on large elastic artery stiffness, oxidative stress-related suppression of NO-mediated EDD, and NO and ROS production. Ultimately, high-resistance IMST may prove to be an invaluable supplement to existing therapies for any population with above-normal blood pressure.

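### A fall in carotid-femoral PWV is equated with improved arterial stiffness and read as a driver of the BP fall, but the raw comparison cannot separate a wall change from the passive effect of lower pressure

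*Protocol article*

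**What the plan says.** In the protocol article, Other Hypotheses predicts that training will "Improve large elastic artery stiffness (i.e., PWV_CF_ reduction"), so a PWV fall is taken as improved stiffness. The last paragraph of the Introduction and the first paragraph of the Discussion place arterial stiffness among the mechanisms behind the BP reduction. The end of the Discussion says that the completed study will determine "the mechanisms driving IMST-induced reductions in BP, including effects on large elastic artery stiffness". Study Design calls the trial mechanistic.

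Under Arterial Stiffness, "PWV_CF_ will be calculated from difference in carotid-sternal and femoral-sternal distance (m) divided by difference in transit time (s"). No pressure term enters. Under Statistical Analysis, "The same statistical approach will be used to address all hypotheses" and "Models will adjust for stratification on OSA severity, sex, and age". The section on randomization and blinding adds to the stated terms by "including CPAP and treatment-by-CPAP interaction effects in the mixed effects models". BP appears in none of these places.

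The Primary Hypothesis expects high-resistance training to lower casual systolic BP "by an average of 15 mmHg; some BP reduction will persist after 4, but not 12 weeks of free living". Other Hypotheses expects diastolic BP to fall too. For flow-mediated dilation the article does handle the stimulus: shear is computed and "if group- or timepoint-differences exist, FMD_BA_ will be adjusted accordingly".

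**The concern.** PWV rises with distending pressure as well as with wall stiffness. This is general physiology and not a figure from the article, so its size is treated below as an assumption. If the primary hypothesis is true, PWV should fall somewhat in the high-resistance arm even if the wall is unchanged. Read as Other Hypotheses words it, that fall would count as improved stiffness. Read as the Discussion words it, it would then be offered as a cause of the very BP fall that produced it.

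Follow-up does not resolve this. BP and the other effects are all predicted to persist in part at 4 weeks and to be gone by 12. A purely passive PWV change would follow the same course and could look like corroboration.

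At stake is one mechanistic conclusion. PWV is listed under Other Outcomes, and the primary and secondary analyses are not affected.

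**Working it through.** **1. The plan's own figure.** Sample Size Calculation and Power states over 80% power with 45 completers per arm at an effect size of 0.63, for any outcome; Statistical Analysis sets a two-sided 5% level. The noncentrality is 0.63 × √(45/2) = 2.99. The normal approximation gives Φ(2.99 − 1.96) = 84.8%, and the noncentral t gives 84.0%. The figure reproduces and is not in dispute.

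**2. Rejection by the raw comparison with no wall change.** From the article: 45 per arm, two-sided 5%. Assumed, because the article gives no figures:
- between-arm fall in mean pressure, F: 5-10 mmHg
- passive slope, b: 0.03-0.08 m/s per mmHg
- residual SD of PWV change, s: 1.0-2.0 m/s
- SD of mean-pressure change: 7 mmHg

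Formulas: passive difference D = b × F; total SD = √(s² + (7b)²); effect size = D / total SD; rejection probability from the noncentral t with 88 df.

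| b | F | s | D (m/s) | Total SD | Effect size | Rejects |
|---|---|---|---|---|---|---|
| 0.03 | 5 | 1.0 | 0.15 | 1.02 | 0.15 | 11% |
| 0.03 | 5 | 1.5 | 0.15 | 1.51 | 0.10 | 7% |
| 0.03 | 5 | 2.0 | 0.15 | 2.01 | 0.07 | 6% |
| 0.05 | 7 | 1.0 | 0.35 | 1.06 | 0.33 | 34% |
| 0.05 | 7 | 1.5 | 0.35 | 1.54 | 0.23 | 19% |
| 0.05 | 10 | 1.0 | 0.50 | 1.06 | 0.47 | 60% |
| 0.08 | 10 | 2.0 | 0.80 | 2.08 | 0.39 | 44% |
| 0.08 | 10 | 1.0 | 0.80 | 1.15 | 0.70 | 91% |

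The range is about 6% to 90%. Every setting exceeds 5%, but by little when the fall is small, the slope shallow and the SD large.

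**3. What pressure adjustment does in the ideal case.** Change in mean pressure is added as a covariate, measured without error, with causation running only from pressure to PWV. Simulation (4,000 trials per setting, F = 10, s = 1.0) gives 5.3% at b = 0.05 and 4.7% at b = 0.08, so rejection returns to about 5%.

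**4. Adjustment when pressure is measured with error.** Suppose the measured change carries an error SD of 5 or 7 mmHg on top of a true SD of 7. The reliability is 49/(49 + 25) = 0.66 or 49/(49 + 49) = 0.50, so 34% or 50% of the passive difference survives. At b = 0.08 and F = 10 that is 0.27 or 0.40 m/s. Simulated rejection with no wall change is 18% or 34%; at b = 0.05 it is 10% or 17%.

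**5. Adjustment when stiffness really drives BP.** Suppose a true wall effect of 0.6 m/s, which lowers mean pressure by k = 8 to 12 mmHg per m/s (between-arm fall 4.8 to 7.2 mmHg), with s = 1.0 and other pressure variation of SD 7. The adjusted arm effect is 0.6 × 49/(k² + 49), which is 0.26 m/s at k = 8 and 0.15 m/s at k = 12. Simulated detection is 44% and 28% after adjustment, against about 80% raw. Adjustment hides much of a mechanism that is real.

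**6. Where a pressure reference is available.** Table 2 puts PWV without infusion at V1, PWV with saline at V2, casual BP at V2, and vitals at both. A same-visit pressure therefore exists for each PWV measurement, but at V1 it comes only from the vitals.

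**The case against.** The strongest reply is that the planned test is sound. It is a randomised comparison of PWV change, and if lower pressure lowers PWV, rejecting is correct. The Discussion also gives a reason to want the total effect, since it treats PWV as a predictor of cardiovascular disease. This stands. A reader might infer from the table that the PWV test has an inflated type I error; it does not, for the null of no effect on PWV. The percentages apply only when rejection is read as a wall change.

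A second reply is that the stated covariates are not a closed list. This also stands. A reader might take Statistical Analysis to adjust for severity, sex and age alone, but the randomization section adds CPAP and its interaction. A supportive pressure-adjusted analysis could sit in a fuller document. What the article does fix is the wording that equates a PWV fall with stiffness and the mechanistic reading of it.

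Third, the Discussion admits that mechanisms cannot be settled definitively in every case, and no decision rule turns a PWV fall into a causal claim. This softens the point but does not remove it: the admission is general, and stiffness is then listed among the mechanisms to be determined.

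Fourth, the size is assumption-driven. A reader might infer that rejection is at least double the nominal 5% throughout. That holds only if the residual SD is fixed near 1.0 m/s; the lowest setting gives 7% at SD 1.5 and 6% at SD 2.0. The expected 15 mmHg is stated for high-resistance training and not as a between-arm difference, and the article says that both programs may affect outcomes. If mean pressure fell by 5 mmHg in the high arm and 3 mmHg in the low arm, then at slope 0.03 and SD 1.0 rejection is about 6%.

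Finally, a reader might infer that only a difference that survives pressure adjustment may be called stiffness. Steps 4 and 5 of the working show why that rule would mislead in both directions.

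**Conclusion.** The point holds as one of interpretation. The article equates a PWV fall with improved stiffness and treats stiffness as a driver of the BP reduction, while nothing stated in the PWV derivation or model terms deals with the pressure fall that the trial itself predicts. The raw comparison answers whether training changes PWV. It does not answer whether the wall changed, or in which direction cause runs.

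With no wall change the raw test would reject in about 6% to 90% of trials, given the assumed pressure fall, slope and SDs; none of those inputs is in the article. The direction of the problem is clear, but its size is not established. The documents do not support calling the test invalid, nor treating the pressure-adjusted result as the true one. This is a worthwhile, low-cost improvement to an Other Outcome.

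**What to change.** - Keep raw PWV as the randomised comparison.
- Add one prespecified supportive analysis with mean arterial pressure, recorded at the same visit as PWV, as a time-varying covariate in the mixed model. Name the source: vitals at V1 for PWV without infusion; vitals or casual BP at V2 for PWV with saline. Casual BP is taken seated, and the article does not describe the posture or timing of vitals, so state how the reference pressure is obtained.
- In Other Hypotheses, replace the parenthesis after stiffness with wording such as: *carotid-femoral PWV will fall; a fall in unadjusted PWV does not by itself separate a change in arterial stiffness from the effect of lower pressure, and will not by itself be reported as a mechanism of the BP reduction.* Align the mechanism sentences in the Introduction and Discussion.
- Report both results with their limits. Do not make the adjusted result a gatekeeper, and do not relabel a fall that disappears on adjustment as a consequence of lower BP.

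Cost: one extra analysis and a few sentences, and possibly a tighter specification of the V1 pressure reading. The adjusted analysis has less power and is supportive only, because pressure is a post-randomisation variable.
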